#### Intervention translation and validation

The scale has been validated in Dutch and found to correlate significantly with the Saint George Respiratory Questionnaire (SGRQ), the Standardised Asthma Quality of Life Questionnaire (AQLQ-S), and the Audit of Diabetes Dependent Quality of Life Questionnaire (ADDQoL19) [6]. It has also shown high internal consistency and good test–retest reliability [9].

The protocol includes steps to translate and validate the Dutch ABCC tool into German and Italian versions. The creators of the ABCC tool, developed with funding from ZonMw, a Dutch funder, granted permission for free use in both research and routine patient care.

A Dutch scientific service provider will assist with the cross-cultural adaptation of the ABCC questionnaire because of the team’s limited Dutch proficiency. A forward–backward translation procedure will be applied, involving independent translations into Italian or German and back-translations into Dutch. Post-translation cognitive interviews with a small group of chronically ill individuals will assess the content validity from the patient’s perspective.

To validate the translated ABCC tools, we will employ the “COPD Population Screener™” (COPD-PS™) and the “Asthma Control Test™” (ACT™) [14], both available in Germany and Italy [15, 16], to evaluate convergent validity. For T2DM patients, we will use the “European Quality of Life 5 Dimensions 5 Level” (EQ-5D-5L) questionnaire, while the “Kansas City Cardiomyopathy Questionnaire” (KCCQ) will be used for heart failure patients. In both cases, validated German and Italian versions are available [17–20]. Following the use of disease-specific measures for each condition, the approach to validating the convergent validity of the ABCC tool will be to analyze correlations between ABCC tool scores and these established non-ABCC measures.

We aim to include 30 persons per disease group in line with the initial ABCC scale validation in the validation study. Eligible patients are those diagnosed with COPD, asthma, T2DM, and/or heart failure who are 18 years or older and comprehend and read German or Italian. As the ABCC tool is a monitoring tool and not a diagnostic tool, both new and existing patients are suitable. To ensure participant stability at baseline, those who had taken prednisone for asthma or COPD exacerbation or were hospitalized for T2DM or heart failure, within 6 weeks prior to the start of the study will be excluded.

### Criteria for discontinuing or modifying allocated interventions {11b}

Given that the ABCC tool is used and then the participant is followed up with measurements for up to 1 year, the criteria for discontinuation of the intervention itself are as follows: (i) participants have the right to withdraw their consent at any time, for any reason. If a participant wishes to discontinue the use of the ABCC tool after it has been administered but before the follow-up period, their request should be honored. (ii) If a participant experiences significant emotional distress during the initial administration of the ABCC tool that cannot be adequately addressed, intervention discontinuation is warranted. (iii) If a participant’s health status changes significantly immediately after using the ABCC tool such that the tool is no longer appropriate or relevant, discontinuation of the intervention might be necessary. (iv) If a technical error occurred during the initial administration of the ABCC tool that rendered the results invalid or unusable and it is not feasible to re-administer the tool, discontinuation of the intervention might be the best course of action.

In cases where discontinuation of the ABCC tool intervention is being considered, the decision will be made through a collaborative process involving the participant and their GP. The coordinating center is available to provide guidance and support in this decision-making process, ensuring compliance with study protocols and ethical standards.

### Strategies to improve adherence to interventions {11c}

Adherence to the ABCC intervention and follow-up measurements will be improved and monitored by (i) ensuring that participants understand the importance of the ABCC tool and the role played by their participation in the research. This includes explaining the purpose and benefits of the tool, the potential impact of the research on healthcare, and how their contributions can make a difference. (ii) Regular contact with the participants should improve adherence. Reminders about upcoming follow-up measurements will be sent, checking in with participants to see how they are doing and answering any questions they may have. (iii) The Dutch ABCC tool is easy to use and visually appealing. The tool will be used in the South Tyrol study with an identical design to encourage its use. (iv) The tool is easily accessible to all participants regardless of their technological expertise or resources. This will involve providing options for in-person, phone, or online follow-up if possible. (v) Monitoring adherence is digitally tracked and follow-up calls are made. All strategies will comply with ethical guidelines and data protection regulations, and respect participant confidentiality and autonomy.

### Relevant concomitant care permitted or prohibited during the trial {11d}

All concomitant care and interventions will be reported in this study. The primary concern is the safety and well-being of participants. If treatment intervention or care is necessary for the participant’s health, it will not be prohibited, even if it may potentially impact the trial results. The trial management team will regularly monitor and review concomitant care and interventions. This will help identify any potential interactions with ABCC intervention. Participants, caregivers, and the healthcare team will be educated about concomitant care and interventions, which will help ensure compliance and protect the participants’ health. All instances of concomitant care and intervention will be thoroughly documented.

### Outcomes {12}

#### Primary outcome

The primary objective of this study is to assess changes in perceived quality of care over an 18-month period using the Patient Assessment of Chronic Illness Care (PACIC) [20, 21] as the comparative measure. This assessment will be administered at baseline and then at specified follow-up points to determine changes from usual care in the cohort of participants.

#### Secondary outcomes

Secondary objectives encompass several areas:

Assessing the shift in perceived quality of care, employing the PACIC, against regular care after 18 months, individually for each chronic condition.We evaluate variations in perceived quality of care, gauged by the PACIC, against regular care at 6- and 12-month intervals for both the entire participant group and each chronic condition individually.Evaluate changes in universal health-related quality of life, as gauged by the EQ-5D-5L [21, 22], in comparison with standard care at 6-, 12-, and 18-month intervals for the entire participant group and for each chronic condition separately.Scrutinizing changes in participant activation, as measured by the Patient Activation Measure (PAM) [23, 24], against standard care at 6-, 12-, and 18-month intervals for both the entire participant group and for each chronic condition.Conducting practice-level analyses to evaluate the overall impact of the ABCC tool on healthcare delivery and outcomes. This includes assessing changes in practice-wide metrics for average improvements in PACIC scores, EQ-5D-5L outcomes, and PAM levels, comparing the aggregated results of the intervention group practices against those of the control group practices.

In addition, we will assess the cost-effectiveness of the ABCC tool compared with usual care after an 18-month period. This analysis focuses on the direct medical costs reimbursed by the National Health Service (NHS). The economic resources claimed will be obtained from the data of general practitioners, the health administration of the province, and the South Tyrolean ambulance service. Only costs and benefits from the healthcare perspective are considered and will include the following:

Pharmaceutical treatments for chronic disease(s): The cost of purchasing branded medicines will be determined from national price lists, with public prices used after subtracting the discounts prescribed by the Agenzia Italiana del Farmaco (AIFA). For generic medicines, we used prices from the AIFA transparency list, which lists medicines reimbursed by the NHS, based on the reference price system.Hospitalization for chronic disease(s): Costs are determined using the latest national DRG tariff system of the Italian Ministry of Health. This system quantifies resource use and provides an estimate of the cost per acute event from an NHS perspective.Outpatient specialist visits and examinations for chronic disease(s): Costs will be based on the latest available “National Tariff Nomenclator.”General Practitioner (GP) visits for chronic disease(s): Costs are taken from Dal Negro et al. [25] and extrapolated to current prices according to the ISTAT consumer price index.

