### Implementation {16c}

Participant enrollment and group allocation will be managed directly by the research team. After generation of the random allocation sequence, practices will be notified of their assignment to either the intervention or control group. Necessary equipment, including a tablet PC loaded with the ABCC tool, along with instructions for use, will be provided to practices in the intervention group to ensure a clear and efficient setup for the conduct of the study.

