First, the implementation of the ABCC tool in general practice is a key operational aspect of this study. Given that the tool is new to the South Tyrolean Health Service, its integration within the clinical workflow of different practices might pose a challenge [33]. It will be crucial to ensure appropriate training for general practitioners and their teams to effectively use the tool and interpret results. Our implementation strategy for the ABCC tool within general practices aims to seamlessly integrate its use during face-to-face consultations. General practitioners will review the results of the ABCC tool with participants immediately, utilizing it as a dynamic component of the patient-provider interaction. This immediate feedback mechanism is designed to enhance shared decision-making and encourage patient self-management in real-time. Furthermore, while the tool is intended to be a valuable resource throughout the patient–provider relationship, its use in each visit will be at the discretion of the healthcare provider, based on the relevance to the patient’s current care needs and consultation focus. This flexible approach aligns with our goal to validate the effectiveness and cost-effectiveness of the ABCC tool in enhancing perceived quality of care and quality of life, as observed in Dutch studies, within the distinct context of the South Tyrolean healthcare system. Successful integration and positive outcomes from this study will inform broader implementation strategies, aiming for a patient-centered and economically beneficial tool across healthcare settings.

Second, the recruitment of a diverse range of general practices, both urban and rural, across different language groups is fundamental to the generalizability of the results [34]. Achieving this diversity might be challenging, given the voluntary nature of participation. Moreover, within each practice, it is important to ensure a balanced representation of patients with different chronic conditions that requires careful management and supervision. To ensure a balanced representation of patients with different chronic conditions within each practice, we will engage with general practitioners to promote the enrollment of a diverse patient cohort. This strategy complements the stratified randomization process, aiming to achieve a comprehensive assessment of the ABCC tool’s impact across the spectrum of chronic conditions addressed in our study.

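### The listed cost items include nothing for delivering the ABCC tool; unless the health economic evaluation plan adds it, incremental cost is understated in the tool's favour

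*Protocol article*

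**What the plan says.** The Secondary outcomes section sets the frame of the economic analysis as direct medical costs that the NHS reimburses. Resource use is to come from "the data of general practitioners, the health administration of the province, and the South Tyrolean ambulance service". The cost list opens with "Only costs and benefits from the healthcare perspective are considered and will include the following" and has four items, each with its price source:

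- medicines (national price lists net of the regulator's discounts, and the reference-price list for generics)
- hospital stays (national DRG tariffs)
- outpatient specialist visits and examinations (national tariff schedule)
- GP visits (unit cost from a published costing study, indexed to current prices)

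Other sections describe what delivering the tool requires. Implementation {16c} provides intervention practices with "Necessary equipment, including a tablet PC loaded with the ABCC tool". Intervention description {11a} describes an online portal and a shared decision-making discussion. The Discussion says "It will be crucial to ensure appropriate training for general practitioners and their teams", has GPs go through the results in the consultation, and foresees possible custom work to link the app to patient records. Intervention translation and validation records that use of the tool is free of charge.

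The Cost-effectiveness analysis section adds decision modelling, repeats the focus on direct medical costs together with QALY gains, and leaves detailed methods to a separate health economic evaluation plan.

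**The concern.** A cost-effectiveness comparison has to charge the new strategy for what it takes to provide it. Here the resources specific to the tool arise in one arm only, and no listed item captures them, while any downstream saving in medicines, admissions or visits would be credited to the tool.

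The protocol hypothesises that the tool will be cost-effective (Discussion) and intends to bring it into primary care if it proves effective (Objectives {7}). Whoever decides on adoption would have to provide the delivery resources, so a result that leaves them out answers a different question.

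A second, smaller point is that the ambulance service is one of three named data sources, yet no ambulance item is on the cost list.

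**Working it through.** The documents give no unit cost, cost difference, QALY difference or cost-effectiveness ratio, so there is no stated figure to reproduce. The check sets the sections side by side and then works out the direction of the effect.

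**1. Delivery resources against the cost list**

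| Resource | Where described | Captured by a listed item? |
|---|---|---|
| Permission to use the tool | Intervention translation and validation | Free, so nothing to cost |
| Tablet PC | Sequence generation {16a}; Implementation {16c} | No |
| Online platform, support, record linkage | Intervention description {11a}; Discussion | No (no fee stated) |
| Training of GPs and teams | Discussion | No |
| Extra GP visits | Secondary outcomes | Yes, as GP visits |
| Longer GP visits | Discussion | No: a fixed unit cost prices a long and a short visit alike |
| Ambulance use (both arms) | Secondary outcomes, as a data source | No |

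The count is four cost items, none for delivery and none for ambulance use.

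**2. Direction of the delivery omission**

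Let D be the between-arm difference in the four listed costs, c > 0 the unlisted delivery cost per intervention patient, and Q > 0 the QALY gain.

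- Incremental cost as listed is D. With delivery it is D + c.
- Cost per QALY as listed is D/Q. With delivery it is (D + c)/Q. The understatement is c/Q.
- If D lies between −c and 0, the list shows a saving although total cost has risen. This needs no assumption about QALYs.

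The sign is fixed because c arises in one arm only.

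**3. Illustrative size (all euro and QALY values assumed)**

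The one input from the protocol is the average of 10 patients per practice (Sample size {14}). Assume a fixed delivery cost of EUR 200 to 1,500 per practice and staff time of EUR 0 to 60 per patient:

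- low: c = 200/10 + 0 = EUR 20
- high: c = 1,500/10 + 60 = EUR 210

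With an assumed gain of 0.01 to 0.05 QALY:

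- smallest understatement: 20/0.05 = EUR 400 per QALY
- largest understatement: 210/0.01 = EUR 21,000 per QALY

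The range is too wide to say whether a decision would change.

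**4. Ambulance use**

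Both arms use ambulances. With an assumed between-arm difference of −0.2 to +0.2 trips per patient and an assumed EUR 300 per trip, the omitted cost difference is −0.2 × 300 = EUR −60 to +0.2 × 300 = EUR +60. The sign is undetermined.

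**The case against.** The strongest reply is that the article leaves detailed methods to a health economic evaluation plan that is not shown, and that intervention costing, write-off periods and sensitivity ranges belong there. The opening words of the list also restrict the perspective; they do not say that nothing else will be counted. Both points stand. A reader might infer that the plan excludes delivery cost and that the result is therefore already biased; the text does not go that far. The deferral does not remove the concern, however. The article itself fixes the categories and price sources, and the section that announces the evaluation plan repeats the narrow focus on direct medical costs. Tablets, platform and training do not obviously count as NHS-reimbursed medical costs, so a plan that kept to this frame would leave them out.

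Further objections stand in part:

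- GPs are paid per capita (Study setting {9}), so a longer consultation may trigger no extra reimbursement. But the plan already prices GP visits at a unit cost despite that payment system, so it does value GP time.
- The tablet may also be used to complete the study questionnaires (Plans for assessment and collection of outcomes {18a}), so part of its cost belongs to the trial and not to delivery.
- Use of the tool at each visit is at the provider's discretion (Discussion), so added time may be modest.

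Three stronger readings are tempting and should be avoided. First, that only the questionnaire is free: the stated permission covers the tool. Second, that the intervention arm is charged for none of its own resources: extra GP visits are counted. Third, that the missing ambulance item also favours the tool: if the tool reduced ambulance use, the omission would work against it.

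**Conclusion.** The point holds in conditional form. Followed as written, the cost list understates the intervention arm's cost by the unlisted delivery cost per patient, and the cost per QALY by that amount divided by the QALY gain, always in the tool's favour. This rests on the evaluation plan not adding the item and on delivery cost being above zero. The documents do not allow the size to be calculated; the EUR 400 to 21,000 per QALY range follows from assumed inputs and only illustrates scale.

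The ambulance point is a mismatch within one section between data sources and cost items, with unknown direction. Neither matter affects the primary PACIC analysis.

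**What to change.** Add to the cost list an ABCC delivery cost per intervention patient covering tablet, platform and support, training hours of GPs and assistants, and added consultation time. State the write-off period and the number of patients over whom fixed costs are spread, and separate what serves trial data collection only. Widen the cost frame enough for this item to fit. Carry it into the evaluation plan and the decision model with a sensitivity range.

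Log these resources prospectively. Table 2 schedules direct medical costs only at close-out, and training hours and added consultation time are hard to reconstruct afterwards.

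Reconcile the data sources with the cost list, either by costing ambulance transports at tariff in both arms or by removing the ambulance service as a source.

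The cost is a wording change in the protocol and the evaluation plan, plus a simple project cost log. No new patient-reported data are needed, and Trial status says recruitment had not begun.

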### Participant timeline {13}

Participants’ timeline for this study is as follows (Table 2):

**Table 2 Tab2:** SPIRIT schedule of enrolment, interventions, and assessments of the ABCC South Tyrol study

	**STUDY PERIOD**						
	**Enrolment (Pre-allocation)**	**Allocation**	**Post-allocation (Months)**				**Close-out**
**TIMEPOINT**	***-1***	**0**	***0***	***6***	***12***	***18***	***18***
**ENROLMENT:**							
**Practice agreement**	X						
**Practice allocation**	X						
**Patient eligibility screen**	X						
**Patient informed consent**	X						
**INTERVENTIONS:**							
**Regular Care**			X				
**ABCC Care**			X				
**ASSESSMENTS:**							
**Chronic Condition**		X					
**PACIC**		X		X	X	X	X
**EQ-5D-5L**		X		X	X	X	X
**PAM**		X		X	X	X	X
**Direct Medical Costs**							X

*ABCC* Assessment of Burden of Chronic Conditions, *EQ-5D-5L* European Quality of Life 5 Dimensions 5 Level, *PACIC* Patient Assessment of Chronic Illness Care, *PAM* Patient Activation Measure

#### Enrollment and baseline assessment

The recruitment and enrollment process will begin once the general practices are randomized to either the intervention or control group. Baseline assessments will be conducted for all enrolled participants. This assessment will include measurement of perceived quality of care using the PACIC, evaluation of health-related quality of life using the EQ-5D-5L, and assessment of patient activation using the PAM.

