## Methods: participants, interventions and outcomes

### Study setting {9}

The Health Authority of South Tyrol, a region with a mix of Italian and Austrian cultures, is essentially part of the Italian National Health Service (NHS). In this region, general practices are predominantly independent entities, often run by single practitioners or small groups of GPs who work independently but may share office space. These practices are not typically housed within hospitals or larger medical centers, maintaining a focus on community-based care. Patients are assigned to GPs by the public health service, and GPs are paid on a per capita basis for the number of patients assigned. This study will be conducted in primary care facilities in South Tyrol. Data will be collected from patients in the general practice in this region. Researchers will enroll in general practices with participation from healthcare providers, such as general practitioners and practice nurses. Practice randomization will be stratified. Subsequently, healthcare providers will recruit the patients. This is because both the provider and the patient will either use the ABCC tool (intervention group) or receive standard care (control group). The study outcomes are assessed at the practice and patient levels.

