### Who will take informed consent? {26a}

Informed consent will be obtained by either the General Practitioner (GP) investigator or the General Practice Assistant involved in the study. These individuals will be comprehensively trained on how to obtain their informed consent. This training emphasizes the importance of transparency and open communication during the consent process, the need to respect participant autonomy, and the need to ensure that participants fully understand the study’s implications.

The consent process will involve potential participants who have received an informed consent form approved by the Ethics Committee. This form contains detailed information about the trial, including its purpose, duration, procedures, and associated risks and benefits. Participants will be given the opportunity to read this document alone or with the GP investigator or a General Practice Assistant.

They will be able to ask any questions they may have about the trial and the GP investigator or General Practice Assistant will provide comprehensive answers to these queries. Once the participants are comfortable and have confirmed their understanding of the study, they will be asked to provide written consent to participate. This procedure ensures that the consent obtained is informed, voluntary, and in accordance with the guidelines.

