### Sample size {14}

The sample size estimation was guided by analogous assumptions from a concurrent study conducted in the Netherlands, thereby offering a relevant frame of reference for our calculations. The study’s primary outcome will be determined through the Patient Assessment of Chronic Illness Care (PACIC) measure. Given the lack of substantial data on the minimum significant difference and standard deviation for the PACIC in this specific population, an estimated medium effect size of 0.51 is derived from the work of Slok et al. [26]. This is based on an observed mean difference of 0.49 between the intervention and control groups, and a pooled within-group standard deviation of 0.96 from the same study.

For the current study, using an independent samples *t*-test, a significance level of 0.05 for two-sided testing, a power of 90%, and an even split between intervention and control groups, it is estimated that each group should include 82 patients. However, as patients will be grouped within general practices, this number is adjusted to account for the design effect, which is calculated as 1 + (m − 1) × ICC (intraclass correlation), where an ICC of 0.05 and an average of 10 patients per general practice is assumed [6].

After adjusting for cluster design (multiplication factor of 1.45), variable cluster sizes (division by 0.9), and an anticipated dropout rate of 25% (division by 0.75), it was estimated that each group would require 177 participants. Each group will need to include 18 general practices with an average of 10 patients per general practice. Therefore, 360 participants (180 per group) from 36 general practices (18 per group) will be recruited for this cluster-randomized study.

The aim was to achieve a balanced distribution among the various chronic conditions. However, given that healthcare providers are not explicitly instructed to strive to achieve this balance, this may not be ensured.

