### Concealment mechanism {16b}

In this study, the allocation sequence was implemented using a centralized, computer-generated randomization process. This process will be managed by a dedicated statistician who will not be involved in participant recruitment or intervention delivery, thereby ensuring concealment of the sequence until interventions are assigned.

Once the general practices have been recruited, demographic and practice characteristics (including the preferred language of patients, urban or rural location, and demographic characteristics of the general practitioners) will be collected and entered into randomization software. The software then generates a random allocation sequence, assigning practices to either the intervention group (use of the ABCC tool) or the control group (usual care without the ABCC tool).

The allocation sequence will be kept confidential and will not be disclosed to the general practice or research team involved in the recruitment and follow-up of participants until the assignment point. This approach ensures that the assignment process is not influenced by any pre-existing knowledge or bias and that allocation concealment is maintained throughout the study.

Once the randomization process is completed, each general practitioner will be informed of their group assignment by the central research team and the necessary instructions or equipment (including the tablet PC for the intervention group) will be provided. This method ensured that the allocation process was transparent and unbiased, thereby maintaining the integrity of the study design.

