## Discussion

The South Tyrolean study will examine the effectiveness and cost-effectiveness of the ABCC tool, which is designed to visualize the burden of disease, promote shared decision-making, and encourage self-management. We hypothesize that the ABCC tool will significantly enhance the perceived quality of care and quality of life and will be cost-effective given its successful implementation in the Netherlands. The strength of our study is its pragmatic approach, involving broad inclusion criteria and a variety of outcomes such as patient experience of care, quality of life, and resource utilization. Our study, like Dutch studies, aims to reflect the effectiveness of the tool in real-world implementation, enhancing external validity.

We aim to minimize confounding factors by considering those known to be associated with interventions and outcomes. Patient allocation will be based on general practice cluster randomization and not on patient characteristics, reducing the risk of selection bias. We acknowledge that many of the study outcomes are subjective and dependent on patients’ perceptions. Additionally, as our study will be conducted only in primary care settings in South Tyrol, we may not be able to extrapolate our findings to other care settings or regions.

Given the intricate design of ABCC studies, operational and practical issues warrant discussion.

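### Practice staff who already know their arm recruit and consent the patients, so allocation is not concealed at patient level and the comparison is open to recruitment bias of unknown size

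*Protocol article*

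**What the plan says.** Four sections of the protocol article set the order of events.

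- Study setting {9}: "Practice randomization will be stratified. Subsequently, healthcare providers will recruit the patients".
- Concealment mechanism {16b}: once randomisation is done, "each general practitioner will be informed of their group assignment by the central research team".
- Enrollment and baseline assessment: "The recruitment and enrollment process will begin once the general practices are randomized to either the intervention or control group".
- Section {26a}, on who takes consent, names practice staff: "Informed consent will be obtained by either the General Practitioner (GP) investigator or the General Practice Assistant involved in the study".

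Who will be blinded {17a} states that neither patients nor care providers can be blinded.

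Two assurances are given. The concealment section concludes that "allocation concealment is maintained throughout the study". The Discussion says: "Patient allocation will be based on general practice cluster randomization and not on patient characteristics, reducing the risk of selection bias".

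Two places do not fit this order cleanly. Implementation {16c} says the research team directly manages patient enrolment. Table 2 places the patient eligibility screen and the row "Patient informed consent" under a column headed as pre-allocation, but practice allocation is ticked in that same column.

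**The concern.** Cluster randomisation makes the practices comparable. It makes the patients comparable only if they are identified before anyone choosing them knows the arm, or are chosen by a rule that leaves no discretion. Here the person who approaches and consents a patient knows the arm, and so can the patient who decides whether to accept. A GP with a new tool may approach patients expected to engage with it, while a control GP has no such reason.

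The primary outcome, PACIC, is the patient's own rating of care in an open trial. Rapport with the GP and motivation could plausibly affect both who is recruited and how the score moves over 18 months. A difference in who was recruited would then look like an effect of the tool.

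**Working it through.** **1. Sequence.** Taken together, {9}, {16b}, {26a}, the enrolment section and {17a} give this order: practice randomised, GP told the arm, practice staff recruit and consent, baseline taken, intervention starts. The concealment described in {16b} protects the practice-level sequence up to the point of assignment. It ends before any patient is recruited, so the claim that it lasts throughout the study fails at patient level.

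**2. Limits on whom staff approach.** The article describes no blinded recruiter, consecutive sampling or patient list fixed before randomisation. On disease mix, Sample size {14} says "healthcare providers are not explicitly instructed to strive to achieve this balance", while the Discussion says GPs will be encouraged to enrol a diverse cohort. Neither statement constrains which eligible patient is invited.

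**3. What the analysis can repair.** The potential confounders in {20a} are demographic factors, BMI, smoking, multimorbidity and practice features. Motivation, disease severity and patient activation are not listed, although the Patient Activation Measure is collected at baseline. Confounders are kept by a p ≤ 0.05 screen, and inverse probability of treatment weighting ({20a}, {20b}) balances observed covariates only. Baseline PACIC can absorb a stable difference in level. It cannot absorb selection of patients who are more likely to improve.

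**4. Plan's sample size reproduced.** Inputs from {14}: difference 0.49, SD 0.96, two-sided alpha 0.05, power 90%, ICC 0.05, 10 patients per practice, 0.9 for variable cluster size, 25% dropout.

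- Effect size: 0.49 / 0.96 = 0.51. The t-test needs 81.8, so 82 per group, as stated.
- Design effect: 1 + (10 − 1) × 0.05 = 1.45.
- 82 × 1.45 / 0.9 / 0.75 = 176.1, so 177 per group, as stated. The plan rounds this to 180 in 18 practices.

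**5. Standard error implied by the plan.**

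- Effective n per arm: 180 × 0.75 × 0.9 / 1.45 = 83.8.
- SE = 0.96 × √(2 / 83.8) = 0.148 PACIC points.

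**6. Illustration of bias.** The documents give no figure, so the shift is an assumption. Let b be the shift left in the change in PACIC by differential recruitment, with no true effect. Type I error = P(|Z + b/SE| > 1.96).

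| Shift (SD) | b = shift × 0.96 (points) | Share of 0.49 | Type I error |
|---|---|---|---|
| 0 | 0 | 0% | 5% |
| 0.05 | 0.048 | 10% | 6.2% |
| 0.10 | 0.096 | 20% | 9.9% |
| 0.20 | 0.192 | 39% | 25.3% |

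The SE comes from a single-time two-group comparison in the sample-size section. The documents give no SD for the change, so the table shows scale and is not a forecast.

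**The case against.** The strongest counter-argument concerns the outcome. It is change in PACIC, with a baseline measurement and a mixed model containing a group-by-time term. If intervention GPs simply recruited more satisfied patients, a constant difference in level would already be present at baseline and would cancel in the change. This stands, and it limits the illustration: the error rates apply only to a shift that survives in the change. It does not remove the risk, because selecting patients who are readier to respond affects the change itself.

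It is also fair that {20a} recognises that patients are not individually randomised and plans adjustment and weighting. The Discussion claims only that the risk of selection bias is reduced. The ethics-approved full protocol is not shown and may fix an order of approach. The absence of such a rule from a condensed article is therefore not itself the point. The point rests on the stated sequence and on the concealment claim that contradicts it.

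A reader might infer three further things that the text does not support.

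- **GPs hand out the baseline questionnaires.** No section says so. Under {18a} the research team facilitates completion by telephone or email, with the practice tablet as an option. The text supports only that baseline follows allocation, in patients who can know their arm.
- **Table 2 already shows patients consented, with baseline completed, before allocation.** It does not. Practice allocation is ticked in the same column as patient screening and consent and is listed above them, and baseline PACIC sits one column later, under allocation. The table is ambiguous.
- **GPs are invited to steer recruitment by arm.** The Discussion's encouragement of a diverse cohort applies to all practices and concerns disease mix.

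**Conclusion.** The point holds as a design weakness joined to a wrong statement. Patients are recruited and consented after practices know their arm, so the claim that concealment is maintained throughout is incorrect at patient level. The Discussion's assurance on selection bias covers how practices are assigned and does not cover who is recruited.

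Bias can enter the primary comparison. The documents do not show that it will, or how large it would be. At the implied SE of 0.148, an assumed residual shift of 0.05 to 0.20 SD in the change would raise type I error to about 6% to 25%. The lower end is almost harmless and the upper end is serious, and nothing in the article narrows the range. Larger assumed shifts would give larger error rates, but the documents supply no basis for them.

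**What to change.** Before recruitment starts:

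1. Have each practice identify eligible patients by the chart review already planned in Eligibility criteria {10}, obtain consent and complete baseline PACIC, EQ-5D-5L and PAM before its allocation is disclosed. Then release the allocation and, in the intervention arm, the tablet.
2. Where that is not possible, have each practice lodge its list of eligible patients with the coordinating centre before randomisation, and approach patients in an order the centre sets.
3. Report numbers eligible, approached and consented by arm.
4. Correct the statements in {16b} and the Discussion: concealment covers the practice-level sequence up to assignment, and protection against selective recruitment depends on steps 1 and 2.
5. Reconcile {9}, {26a} and the enrolment section with {16c} on who enrols patients, and with Table 2, whose pre-allocation column contains practice allocation.

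The sample size stays at 177, rounded to 180, per group. The cost is later release of allocation and tablets, plus steering committee and ethics approval of the change under the protocol-amendments section {25}. Trial status reports that recruitment had not begun, so the change was still cheap at that point. Once patients have been recruited with the arm known, analysis cannot remove unmeasured selection.
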